### Outcome measures

#### Primary outcome measure

The primary outcome will be BSCVA in logMAR units at 3 months. This will be measured by a trial-certified optometrist, independent of all other aspects of the study and masked to allocation. This has been the primary outcome of several other trials and will therefore facilitate comparison. Three months is the time at which clinical experience suggests most corneal ulcers have usually healed. BSCVA is chosen as it is easy to measure and is of functional significance. We will measure the BSCVA using an LED-backlit, Tumbling-E LogMAR chart (Good-Lite, Illinois, USA) under controlled conditions. We will also measure vision using Peek Acuity, a validated smartphone application, in situations where the patient is unable to attend the hospital for follow-up and outcome data is only available through a domiciliary visit.^29^ For patients who have counting fingers (CF) vision or less, predefined logMAR values will be assigned based on previous clinical trials.^30 31^ Similarly, for patients who undergo a corneal transplant (TPK), a predefined visual acuity of 1.9 logMAR will be given, or last observation carried forward (whichever is the better vision), as per previous studies.^6^

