### Outcome assessments

Participants will be reassessed at 2 days, 1 week, 2 weeks, 3 weeks, 2 months and 3 months following enrolment. Additional examinations, outside the trial protocol schedule may be conducted by the supervising clinician as indicated. The specific assessments to be carried out at each visit are indicated in table 3. These will be conducted in the same way described for the baseline assessment as described (table 2). At each follow-up assessment, the participant will be asked about adherence to treatment and symptoms, including side effects, if still receiving trial treatment. This will be recorded in the case record file. To monitor trial medication adherence, the study participants will be asked to bring their eye-drop bottles to the 1-week, 2-week and 3-week follow-ups. The amount of remaining medication will be measured by weighing the bottle and will be compared with the anticipated remaining amount provided the drops were being used as instructed, resulting in a ratio of actually remaining to what is anticipated. Participants will be resupplied with medication as needed. The presenting visual acuity will be measured on each visit. In addition, the BSCVA will also be measured at the 3-month follow-up (primary outcome measure). At the final 3-month follow-up, the three quality of life questionnaires will be repeated. On each occasion the eyes will be examined using a slit-lamp and the cornea photographed. The IVCM will be repeated at 1, 2 and 3 weeks to determine whether there is evidence of fungal hyphae resolution with the fragmentation of linear elements. At the 1-week follow-up if the ulcer has not healed it will be rescraped for repeat culture to determine whether the keratitis is now culture positive or culture negative. We will give the study participants appointment cards for the next follow-up and they will be reminded about the follow-up a week prior to the date. Public transport costs will be paid for participants who are outpatients.

**Table 3 T3:** Baseline and follow-up assessment components

Assessment item	Baseline	Day 2	Day 7	Day 14	Day 21	Day 60	Day 90
History/baseline questionnaire	X						
Check treatment adherence		X	X	X	X	X	X
Check for side effects		X	X	X	X	X	X
Visual acuity—presenting	X	X	X	X	X	X	X
Visual acuity—BSCVA	X						X
Contrast sensitivity	X						X
Slit-lamp examination	X	X	X	X	X	X	X
Cornea photography	X	X	X	X	X	X	X
In vivo confocal microscopy	X		X	X	X		
Cornea samples (microbiology/PCR)	X		X				

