#### Secondary outcome analysis

The secondary outcomes outlined above and detailed in table 4 will be analysed by arm. Additional adjustment for factors imbalanced between arms at baseline will be introduced as appropriate. Continuous outcomes will be analysed using linear regression. Binary and ordinal outcomes will analysed using logistic regression. Details of these are given in table 4.

**Table 4 T4:** Secondary outcome measures that will be investigated as part of the trial, together with analysis details

Secondary outcome measure	Details
Three-week BSCVA	We will analyse the secondary outcome of 3 weeks BSCVA in logMAR in the same manner as the primary analysis of the primary outcome described above. The 3 weeks BSCVA will include values taken between 18 days and 5 weeks, with the value closest to 3 weeks used.
Presenting VA by Peek	We will analyse the presenting VA by Peek Acuity with and without pinhole at 3 months as a secondary outcome. This will be of interest if we are unable to get reliable BSCVA measurements at 3 months (ie, if patients fail to attend and we need to attend their houses for visual acuity testing). This will be performed in the same way as the primary analysis of the primary outcome. We will also perform a sensitivity analysis including those lost to follow-up, by using the most recent observation of this variable.
Scar/infiltrate size at 1 week, 3 weeks and 3 months by slit lamp examination	The geometric mean of the two principle axes in mm of the scar or infiltrate at 1 week, 3 weeks and 3 months will be used as a secondary outcome variable. The slit-lamp scar size will be compared at each of these time points between treatment arm in the same manner as described above. This will be by linear regression, with treatment arm and baseline infiltrate/scar size as pre-specified covariates. This controls for the baseline infiltrate/scar size.
Time to full epithelial healing (slit lamp examination by ophthalmic clinician)	Time of re-epithelialisation will be defined as the midpoint between the last review where an epithelial defect (ED) was present and the subsequent review where there was no ED. An area of fluorescein staining of less than 0.5 mm will be considered as a resolved ED due to the difficulty in differentiating a smaller defect from a small amount of fluorescein pooling observed in a healed defect.

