	Analysis of time to healing will use Cox proportional hazards regression with treatment group as the primary predictor and with predictors of baseline ED size (using the geometric mean in mm as outlined above). Survival curves will be plotted using Kaplan-Meier analysis for both treatment arms up to the final visit at 3 months. The proportional hazards assumption will be checked by stratifying on quartiles of the baseline ED size and if the assumption does not hold, the stratified results will be the ones reported. Additionally, treatment failure (defined as persisting epithelial defect greater than 0.5 mm at the 3 month review) will be compared between treatment groups using Fisher’s exact test.
Rate of healing	We will assess how quickly the area of ulceration reduces over time. The rate will be calculated between the 1-week, 3-week and 3-month review by taking the difference in ED size between the two time points, in mm, and diving by the number of days to give a rate of mm/day. Analysis will be performed using Cox regression.
Microbiological cure	Patients who have a persisting corneal ulcer (as defined by the presence of an ED) at day 7 will undergo a repeat corneal scrape and microbiological investigations. Microbiological cure at 7 days will be defined as the absence of any micro-organisms as no significant growth on culture. The number of patients with microbiological cure at day 7 will be compared between the two treatment arms using logistic regression with treatment group and organism (*Aspergillus* spp, *Fusarium* spp, or other) as covariates.
Ulcer depth at 1 week and 3 weeks (slit lamp examination by ophthalmic clinician)	The depth of ulcer in terms of percentage of healthy cornea will be compared at 1 week and 3 weeks between treatment arms, adjusting for baseline depth in the same manner with analysis performed by linear regression
Hypopyon height at 1 and 3 weeks, (slit lamp examination by ophthalmic clinician)	The hypopyon height in mm will be compared at 1 week and 3 weeks between treatment arms, adjusting for baseline hypopyon height in the same manner with analysis performed in the same way (linear regression)

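### Table 4's rate of healing from 3 weeks to 3 months is, for most eyes, only the week-3 defect divided by about 69 days, and it can favour the slower-healing arm

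*Protocol article*

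**What the plan says.** The Rate of healing row of Table 4 (protocol article, Secondary outcome analysis) states its aim as "We will assess how quickly the area of ulceration reduces over time". It names the reviews: "The rate will be calculated between the 1-week, 3-week and 3-month review". The value is obtained by "taking the difference in ED size between the two time points, in mm, and diving by the number of days", and then "Analysis will be performed using Cox regression". The row does not end the interval at closure, say what happens to eyes already closed, or adjust for the size of the epithelial defect (ED) at the start of the interval.

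Three other places bear on this:

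- Primary outcome measure: "Three months is the time at which clinical experience suggests most corneal ulcers have usually healed".
- The time-to-healing row of Table 4 counts staining under 0.5 mm as resolved. It also defines a closure time, the midpoint between the last review with a defect and the next without, but only for that separate outcome.
- Outcome assessments, on scheduled visits: "On each occasion the eyes will be examined using a slit-lamp and the cornea photographed". A day-60 slit-lamp reading therefore exists, but the rate does not use it.

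**The concern.** A defect can shrink only while it is open, yet the denominator counts every calendar day between the two reviews. Once an eye is closed at 3 months, its last-interval rate depends only on how large the defect still was at week 3. A larger residual defect gives a higher rate. An eye that had already closed by week 3, which is the better result, gives zero.

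At stake is a secondary efficacy result pointing the wrong way. In a trial asking whether chlorhexidine is non-inferior, a higher late healing rate in one arm could be read as support for it when that arm was simply further behind at week 3. It could also contradict the time-to-healing result reported in the same table.

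**Working it through.** The protocol gives no figure for the rate of healing, so there is none to reproduce. It also gives no ED sizes beyond the entry rule (over 1 mm) and no closure speeds. Those used below are assumptions.

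**Interval lengths (Table 3 visit days).** Week 1 to week 3: 21 − 7 = 14 days. Week 3 to month 3: 90 − 21 = 69 days.

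**One eye.** Take a 2 mm defect at day 21 that is closed by day 90. The written rate is (2 − 0)/69 = 0.029 mm/day, whenever it closed. Speed over the days it was open:

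| Closes on day | Open days after day 21 | Speed while open (mm/day) | Open share of 69 days |
|---|---|---|---|
| 28 | 7 | 2/7 = 0.29 | 10% |
| 35 | 14 | 2/14 = 0.14 | 20% |
| 42 | 21 | 2/21 = 0.095 | 30% |
| 60 | 39 | 2/39 = 0.051 | 57% |
| 90 | 69 | 2/69 = 0.029 | 100% |

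**Direction between arms.** Writing ED21 and ED90 for mean defect size at days 21 and 90:

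mean rate (slow) − mean rate (fast) = [(ED21 slow − ED21 fast) − (ED90 slow − ED90 fast)]/69.

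The slower arm scores higher exactly when the gap in ED size narrows between week 3 and month 3. If most eyes in both arms end at zero, the gap normally narrows.

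**Worked pair.** Baseline 4 mm, constant speeds of 0.15 and 0.10 mm/day. At day 21 the defects are 4 − 3.15 = 0.85 mm and 4 − 2.10 = 1.90 mm; both are closed by day 90. Written rates: 0.85/69 = 0.0123 (fast) against 1.90/69 = 0.0275 (slow). The order is reversed.

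**Simulated arms.** Assumptions: baseline ED lognormal, median 3.5 mm, log-SD 0.4; linear closure; median speeds 0.15 and 0.12 mm/day, log-SD 0.5; under 0.5 mm counted as closed; 400,000 eyes per arm.

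| Week 3 to month 3 | Faster arm | Slower arm |
|---|---|---|
| Already closed at week 3 | 53% | 41% |
| Written rate, all eyes (mm/day) | 0.0143 | 0.0188 |
| Written rate, eyes open at week 3 | 0.0307 | 0.0317 |
| True speed, eyes open at week 3 | 0.119 | 0.103 |
| Mean ED at week 3 (mm) | 1.01 | 1.35 |

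Much of the all-eyes reversal comes from eyes already closed at week 3 scoring zero. Among eyes still open, the gap is only 0.0317 − 0.0307 = 0.0010 mm/day. The all-eyes reversal recurs for 0.20 v 0.15, 0.12 v 0.10 and 0.10 v 0.08 mm/day.

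**Where it does not reverse.** With few closures (linear closure, mean speeds 0.05 v 0.03 mm/day, 59% and 27% closed by 3 months) the written rate is 0.0298 v 0.0249, the right order. With equal median speed of 0.15 and 15% v 25% of eyes never healing (ED held constant), it is 0.0122 v 0.0108, again the right order.

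**The earlier interval.** The 1-week to 3-week rate usually keeps the right order. It reversed only where many eyes had closed by week 3 (linear, 0.30 v 0.20: 0.1075 v 0.1175).

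**The case against.** A reader might infer that the row always ranks the slower-healing arm as faster, so that an inferior drug would necessarily look better. The documents do not support that. The protocol itself says that about a quarter of natamycin-treated infections, or up to 30%, progress to perforation or loss of the eye. If the treatments differ mainly in such failures, the written rate can keep the correct order even with 73–84% of eyes closed by 3 months, which still fits the statement that most have healed. This part of the objection stands, and the claim has to be conditional.

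It is also fair that the figures above compare arithmetic means, whereas the row names Cox regression. They show that the derived value can mislead; they do not show what the named model would report. Changing the model would not restore the missing information, because for eyes closed by 3 months the value is already only the rescaled week-3 defect. The article's general rule is "Continuous outcomes will be analysed using linear regression", so the choice of Cox for a mm/day value needs its own justification, but that is a separate matter.

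The consequence is small. Rate of healing is not in the stated objectives or among the key secondary outcomes in Table 5. Closure is already analysed by Cox regression on time to healing and by Fisher's exact test on persisting defects.

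Finally, handling of closed eyes could be left to an analysis plan that is not shown. That would answer a gap, but the article states the reviews, numerator and denominator outright, and it is that stated rule which fails.

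**Conclusion.** Wrong as written, and minor. For every eye closed at 3 months, which the protocol expects to be most of them, the 3-week to 3-month rate is the week-3 defect divided by about 69 days and holds no information on speed after week 3. This follows from the formula and needs no simulation.

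The direction of the error is conditional. When the arms differ in closure speed and most eyes in both arms close by 3 months, the slower arm can be expected to score higher. In the assumed case the excess is 0.0188 − 0.0143 = 0.0045 mm/day over all eyes. It need not happen if the arms differ mainly in never-healing eyes or if few eyes close. The size rests on assumed ED sizes and speeds.

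Nor should the point be read as touching the non-inferiority conclusion. That rests on best spectacle corrected visual acuity at 3 months, which this row does not enter, and the time-to-healing analysis is likewise unaffected.

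**What to change.** Drop the 3-week to 3-month rate. Compare ED size at week 1 and at week 3 between arms by linear regression, with treatment arm and baseline ED size as covariates, and leave later closure to the existing time-to-healing analysis. Table 4 already uses baseline-adjusted linear regression for scar/infiltrate size, ulcer depth and hypopyon height. In the simulated case, mean ED at week 3 orders the arms correctly (1.01 v 1.35 mm).

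Stopping the clock at closure is the obvious repair, but it should not be used. With the same assumptions and all eyes included, ending the interval at the re-epithelialisation midpoint gives 0.0433 (faster) v 0.0538 (slower), and ending it at the first review without a defect gives 0.0229 v 0.0291. Both remain reversed. Restricting to eyes open at week 3 restores the order with the midpoint (0.0930 v 0.0906), but it compares groups selected by their response to treatment: 100 − 53 = 47% of one arm and 100 − 41 = 59% of the other.

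The cost is a short change to one row of Table 4 and its derivation. No new data are needed, since ED is measured at baseline and at each slit-lamp review. What is lost is one descriptive rate for the late interval.

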### Eligibility criteria

Potential participants need to meet all the inclusion criteria and have none of the exclusion criteria listed in table 1. In summary, they need to have an active FK defined as acute MK characterised by corneal epithelial ulceration (>1 mm in diameter), corneal stromal infiltrate and signs of acute inflammation (eg, conjunctival injection, anterior chamber inflammatory cells, hypopyon) in conjunction with evidence of a filamentous fungal infection on smear microscopy and/or IVCM. There is strong evidence supporting the use of IVCM for diagnosing filamentary FK. Studies have reported sensitivities of 85.7%–89.2% and specificities of between 81.4% and 92.7%, respectively.^26–28^ As some patients will be enrolled on the basis of the results of IVCM which is unable to detect most bacteria reliably, some patients with microscopically confirmed fungal infection will subsequently also be found to have had mixed infection at the time of being recruited into the study, as bacterial cultures may become positive a few days after enrolment. Based on previous experience at SCEH this is likely to account for about 10% of cases. These patients are included in the study but excluded from the primary analysis of the primary outcome (see below). Secondary analyses will include mixed infections.

**Table 1 T1:** Inclusion and exclusion criteria for enrolment in stage 1 (MK cases) and stage 2 (the randomised controlled trial)

Inclusion criteria (all must be met)	Exclusion criteria (any of the following)

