**Stage 2**	
1. Acute MK characterised by:	1. Unwilling/unable to participate in trial and/or attend follow-up
Corneal epithelial ulceration >1 mm diameter	2. Aged less than 18 years
Corneal stromal infiltrate	3. Pregnancy: self-reported, or by urine pregnancy test if uncertain.
Acute inflammation: for example, conjunctival injection, anterior chamber inflammatory cells, hypopyon	4. Breast feeding: self-reported
2. Filamentous fungal hyphae visualised on smear microscopy and/or IVCM	5. Prior topical antifungal treatment
3. Agree to be randomised to either treatment arm and are able to give informed consent	6. No light perception in the affected eye
4. Agree to be followed up at 2 days, 1 week, 2 weeks, 3 weeks, 2 months and 3 months	7. Fellow eye visual acuity <6/60
5. Adults (18 years and older)	8. Acanthamoebic infection visualised by smear microscopy or IVCM
	9. Clinical evidence of herpetic keratitis
	10. Known allergy to study medication (including preservatives)
	11. Previous keratoplasty in the affected eye
	12. Bilateral corneal ulcers
	13. Very severe ulcers warranting immediate evisceration or conjunctival flap
14. Endophthalmitis

IVCM, in vivo confocal microscopy; MK, microbial keratitis.

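### Microbiological cure at day 7 can be observed only in eyes still ulcerated at day 7, so healed eyes cannot count as cured and the comparison between arms can be biased

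*Protocol article*

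**What the plan says.** Two places in the protocol article set the sampling rule, and both limit the day-7 culture to eyes that have not healed. Table 4, under microbiological cure, says "Patients who have a persisting corneal ulcer (as defined by the presence of an ED) at day 7 will undergo a repeat corneal scrape". The Outcome assessments section says "At the 1-week follow-up if the ulcer has not healed it will be rescraped for repeat culture".

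Table 4 then defines the outcome: "Microbiological cure at 7 days will be defined as the absence of any micro-organisms as no significant growth on culture". The analysis follows: "The number of patients with microbiological cure at day 7 will be compared between the two treatment arms using logistic regression". The model adjusts for arm and for the organism grown, the latter in three classes (Aspergillus, Fusarium or other). No denominator is stated, and no rule covers eyes that were not rescraped.

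Entry to the randomised stage does not require a positive culture. Table 1 asks for "Filamentous fungal hyphae visualised on smear microscopy and/or IVCM", and the Eligibility criteria section expects that "some patients will be enrolled on the basis of the results of IVCM".

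The abstract and Table 5 describe the same outcome as a rate of positive cultures at one week, also without a denominator. The Objectives section names reculture at one week among the secondary clinical outcomes.

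**The concern.** The day-7 result exists only for a subset selected after randomisation by something the treatment acts on: epithelial healing is itself an efficacy outcome in Table 4. The patients who respond best leave the sampled group. The eyes that remain in each arm are no longer comparable by randomisation, and the drug that heals more eyes keeps its harder cases.

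There is a second weakness. The definition does not require that anything grew at baseline. An eye that was culture-negative at entry, is still ulcerated and again grows nothing meets the definition whatever the drug did. The covariate list gives such an eye no place, so the analyst must drop it, call it other or add a level, and the OR depends on that choice.

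At stake is the trial's culture-based comparison of antifungal effect, which could come out too small, somewhat too large or, on one reading of the denominator, in the wrong direction.

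**Working it through.** **Plan figure.** The article gives no rate, power or sample size for this outcome, so there is none to reproduce. The target of 500 was set for visual acuity.

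**Assumptions, none from the article.**
- p: proportion truly sterile at day 7, 60% in the better arm and 40% in the other.
- h: proportion healed by day 7; all healed eyes are taken as sterile.
- c: proportion culture-positive at baseline; h is the same in culture-positive and culture-negative eyes.
- For the adjusted model, 50/20/30 Fusarium/Aspergillus/other among culture-positive eyes.

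True OR = (0.60/0.40)/(0.40/0.60) = 2.25.

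**Step 1: selection alone.** Among rescraped eyes the odds of cure are (p − h)/(1 − p).

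| Healed, better v other arm | Odds, better arm | Odds, other arm | OR |
|---|---|---|---|
| 5% v 2% | 0.55/0.40 | 0.38/0.60 | 2.17 |
| 10% v 5% | 0.50/0.40 | 0.35/0.60 | 2.14 |
| 20% v 5% | 0.40/0.40 | 0.35/0.60 | 1.71 |
| 5% v 5% | 0.55/0.40 | 0.35/0.60 | 2.36 |
| 10% v 10% | 0.50/0.40 | 0.30/0.60 | 2.50 |

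Unequal healing in favour of the better drug pulls the OR down, while equal healing pushes it up. With a weaker effect, p = 50% v 40% (true OR 1.50), healing of 20% v 5% leaves (0.30/0.50)/(0.35/0.60) = 1.03.

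**Step 2: baseline culture-negative eyes, no selection.** If they count as cured, the proportion cured is c·p + (1 − c). At c = 70% this is 0.72 v 0.58, an unadjusted OR of 1.86; at c = 85% it is 2.02. The planned model includes organism, however. If these eyes are coded as other, the OR is 1.99 at c = 70% and 2.07 at c = 85%. If they are dropped for lack of an organism, or given their own level, it stays at 2.25.

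**Step 3: both together, unadjusted, c = 70%, healing 20% v 5%.**
- Rescraped eyes only: (0.72 − 0.20)/0.80 = 65.0% v (0.58 − 0.05)/0.95 = 55.8%, OR 1.47.
- All randomised, with unscraped healed eyes as not cured: 52% v 53%, OR (0.52/0.48)/(0.53/0.47) = 0.96, a reversal.

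**Step 4: the proposed analysis.** Restricting to baseline culture-positive eyes and counting healed eyes as not culture-positive returns 60% v 40% and OR 2.25. This holds by construction, since healed eyes were assumed sterile.

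**The case against.** The strongest reply is that the denominator is unstated rather than wrong. The Analysis plan section promises that all patients are analysed as randomised, and the abstract and Table 5 speak of a positive culture rate. Over all randomised patients, a healed eye is then simply not culture-positive, and such coding is often left to the analysis plan. That would be a sound analysis, but it is not what Table 4 defines. Table 4 fixes the sampling rule, the cure rule, the model and the covariates, and under that cure rule a healed eye has no result. A positive-culture rate and a cure rate are complements only if every eye is cultured.

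Three stronger readings are tempting, and the document supports none of them.
- A reader might infer that the effect is necessarily diluted. It is not: dilution needs clearly unequal healing by day 7, and equal healing slightly inflates the OR.
- A reader might infer that baseline culture-negative eyes will be counted as cured and shrink the estimate. The definition allows this, but "logistic regression with treatment group and organism" may equally exclude or separate them, which removes that source of dilution.
- A reader might infer a large bias. The Treatment review section calls antifungal responses slow, so few eyes may have healed by day 7; at 5% v 2% the OR moves only from 2.25 to 2.17.

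It also stands that faster healing is credited elsewhere, through time to epithelial healing, and that this is one of many secondary outcomes.

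**Conclusion.** The point holds in a limited form. As defined, the outcome can be observed only in a subset formed after randomisation and affected by treatment, and the best responders cannot meet it. The place of baseline culture-negative eyes is not settled. The comparison can therefore be biased, most plausibly toward no difference if the better drug also heals more eyes by day 7.

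The size cannot be known from the document. Across the assumed healing rates, a true OR of 2.25 becomes anything from 1.71 to 2.50 through selection alone. It becomes 0.96 if healed eyes are kept as not cured, with 30% culture-negative at baseline and 20% v 5% healed. The definition should be changed before analysis. The primary outcome and the non-inferiority conclusion do not depend on it.

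**What to change.** - **Population:** all randomised patients with a positive baseline fungal culture. This is fixed before treatment, so the comparison stays randomised, and every patient has a value for organism.
- **Outcome:** positive culture at day 7. Eyes with no epithelial defect at day 7 count as not culture-positive; eyes with therapeutic keratoplasty or removal before day 7 count as not cured.
- **Model:** logistic regression on treatment and organism, as now planned.
- **Sensitivity analysis:** Table 4 makes rescraping depend on the epithelial defect alone, whereas the Dosing schedule section's description of a healed ulcer also requires the infiltrate to have resolved. Some unscraped eyes may thus still have active infiltrate. Repeat the analysis without counting epithelialised eyes with persisting infiltrate as culture-negative.
- **Descriptive only:** the comparison among unhealed, rescraped eyes, with the number healed by day 7 in each arm.

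The cost is wording only, with no added visits or samples. The small downside is that healed eyes are assumed, not shown, to be culture-negative.

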### Randomisation and masking

#### Sequence generation

A computer-generated randomisation list will be prepared by an independent statistician at London School of Hygiene and Tropical Medicine (LSHTM), who will hold the sequence, will not be masked, and will not be involved in any other aspect of the trial. The sequence is in a 1:1 allocation ratio of CHX to NATA, with a random block size (2, 4 or 6).

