	For HRQoL, we will use the EQ-5D questionnaire, EQ-Visual Analogue Scale and the WHOQOL-BREF. The EQ-5D is a standardised tool to measure health outcomes.^38^ The WHOQOL-BREF has good applicability in (LMIC as it was developed simultaneously from concept across 18 countries in Africa, Asia and Latin America. It measures four domains of health: Physical Health, Psychological Health, Social Relationships, and Environment. Details of this scoring are given in table 2.^39^
	Analysis will be by comparing the scores obtained for each QoL assessment for the two treatment arms to estimate the effect of CHX and NATA on patients’ QoL. This will be similar to that performed by Habtamu *et al*.^40^ Comparisons between the two medication groups will be adjusted for the matching variables: age and sex. The VRQoL analysis was also adjusted for socio-economic status and the HRQoL analysis adjusted for both socioeconomic status and presence of health problems during the previous 4 weeks, as these factors may confound the association between fungal keratitis and QoL. Logistic, linear and ordinal logistic regression methods will be used for binary, continuous and ordered categorical outcome variable analysis, respectively. Linear regression models and the t-test were employed to compare significant differences in QoL scores and to generate mean and mean differences between the two treatment arms in each QoL subscale and domain, respectively.
Cost-effectiveness analysis, using EQ-5D data from 3 months and direct cost data	Direct cost data will be collected at the 3 months follow-up. Economic costs to the patient can also be calculated from the EQ-5D questionnaire, which will be asked at baseline and at the 3 months follow-up. Mean direct costs incurred by patients will be compared between interventional arms using the t-test for significance. The difference from the baseline EQ-5D and the 3 months EQ-5D mean scores will also be compared in a similar fashion.
Drug adherence	The rate of drug adherence will be compared between the two treatment groups using descriptive statistics.

BSCVA, best spectacle corrected visual acuity; EQ-5D, EuroQol-5 dimensions; LMIC, low-income and middle-income countries; QoL, quality of life; TPK, therapeutic penetrating keratoplasty.

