	2. Pin-hole visual acuity in logMAR at 3 months, trial-certified optometrist
	3. Scar/infiltrate size at 1 week, 3 weeks and 3 months (slit-lamp examination by ophthalmic clinician)
	4. Ulcer depth at 1 week and 3 weeks (slit-lamp examination by ophthalmic clinician).
	5. Hypopyon height at 1 and 3 weeks, (slit-lamp examination by ophthalmic clinician).
	6. Perforation and/or TPK by 3 months (slit-lamp examination by ophthalmic clinician).
	7. Positive culture rate at 1 week
	8. Ocular adverse effects at each follow-up visit (day 2, day 7, day 14, 3 weeks, 2 months, 3 months), slit-lamp examination by ophthalmic clinician
	9. Quality of life (QoL) assessed using: EQ-5D, WHO/PBD-VF20, WHOQOL-BREF (comparison between baseline and QoL measures at 3 months)
	10. Cost-effectiveness analysis, using EQ-5D data from 3 months and direct cost data
	11. Drug adherence at each follow-up visit (day 2, day 7, day 14, 3 weeks, 2 months, 3 months) while the patient is using study medications

EQ-5D, EuroQol-5 Dimension; LMIC, low-income and middle-income countries; MK, microbial keratitis; TPK, therapeutic penetrating keratoplasty.

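### The quality-of-life arm comparison leaves out the baseline score the trial collects, and takes its covariates from a matching and confounding rationale that does not fit a randomised trial

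*Protocol article*

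**What the plan says.** The QoL row of Table 4 (Secondary outcome analysis) compares scores between the two arms and models its method on a cited study. Its adjustment set comes in three parts:

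- For all comparisons: "Comparisons between the two medication groups will be adjusted for the matching variables: age and sex".
- For vision-related QoL: "The VRQoL analysis was also adjusted for socio-economic status".
- For health-related QoL: "HRQoL analysis adjusted for both socioeconomic status and presence of health problems during the previous 4 weeks".

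The reason given for the last two parts is: "as these factors may confound the association between fungal keratitis and QoL". The row then adds, in the past tense: "Linear regression models and the t-test were employed to compare significant differences in QoL scores". No baseline QoL score is listed as a covariate.

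Table 5 (Ethics and dissemination) defines the same outcome as a "comparison between baseline and QoL measures at 3 months".

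The next row of Table 4, on cost-effectiveness, compares mean direct costs by t-test and compares the change in EQ-5D from baseline to 3 months in the same way. It also says: "Economic costs to the patient can also be calculated from the EQ-5D questionnaire".

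**The concern.** The covariates are presented as though the groups had been matched and as though the question were whether fungal keratitis affects QoL. Neither is true of this trial. Meanwhile the covariate most likely to help, the participant's own baseline score, is not listed, although it is collected and Table 5 builds the outcome on it.

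Three things are at stake. The QoL effect would be estimated less precisely than the data allow. A reader could find two EQ-5D arm comparisons with different adjustment and no indication of which one counts. And the report could carry a covariate rationale and a cost source that do not apply.

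**Working it through.** The document gives no power, effect size or correlation for QoL or cost, so there is no stated figure to reproduce. The check compares sections and then sizes the gain under stated assumptions.

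**Matching and confounding.** Sequence generation describes 1:1 allocation in random blocks of 2, 4 or 6. No section mentions matching. Table 1 requires fungal hyphae on smear or confocal microscopy for stage 2, so all randomised participants have the disease. There is no unaffected group, and hence no disease-QoL association in the trial for a covariate to confound. Age, sex and socioeconomic status are legitimate prognostic covariates; their label and justification are what is wrong.

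**Baseline score.** Baseline assessment and Table 3 place all three QoL tools at baseline and day 90. The other continuous outcomes measured at both times use the baseline value: the primary outcome, scar/infiltrate size, ulcer depth and hypopyon height. The QoL row does not, and so departs from both the article's own practice and the Table 5 definition.

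**EQ-5D.** The QoL row gives it a comparison adjusted for age, sex, socioeconomic status and recent health problems. The cost-effectiveness row gives it a t-test on change from baseline. Neither is named as the principal one.

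**EQ-5D as a cost source.** Tables 2 and 4 describe EQ-5D only as a measure of health outcomes. Direct cost data are collected separately at 3 months.

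**Size of the gain.** Let r be the correlation between baseline and 3-month scores. It is not given, so 0.3 to 0.7 is assumed, with equal variances at the two times. Relative to comparing 3-month scores without covariates, the variance of the treatment effect is multiplied by:

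- with the baseline score as covariate: 1 − r²
- with a change score: 2(1 − r)

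For the detectable difference, assume 500 × 0.85 = 425 analysable participants (borrowing the 15% drop-out from Sample size considerations), 212.5 per arm, 90% power and two-sided 0.05. Without covariates it is (1.960 + 1.282) × √(2/212.5) = 0.31 SD. With the baseline score it is 0.31 × √(1 − r²).

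| r | 1 − r² | Variance reduction | 2(1 − r) | Detectable difference with baseline score |
|---|---|---|---|---|
| 0.3 | 0.91 | 9% | 1.4 | 0.30 SD |
| 0.5 | 0.75 | 25% | 1.0 | 0.27 SD |
| 0.7 | 0.51 | 49% | 0.6 | 0.22 SD |

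At each r shown, baseline adjustment has lower variance than either a comparison of 3-month scores without covariates or a change score. Compared with the model actually listed, the gain depends on the partial correlation given age, sex, socioeconomic status and recent health problems, and may be smaller than in the table.

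**The case against.** The strongest reply is that these are wording faults in secondary outcomes. The row does say that it compares the two arms, age and sex are sound covariates whatever they are called, Table 5 does mention baseline, and exact model terms for secondary outcomes are often completed in an analysis plan. Much of this stands, and it limits the point. But the row does not leave the model open: it names a covariate set without the baseline score and gives a reason that cannot apply, so it needs correcting as well as completing.

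Several stronger readings are tempting and are not supported:

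- *The analysis answers a disease-association question.* It does not. The comparison is between the medication groups; only the label and rationale are misplaced. The past tense and the reference to a cited study suggest carried-over wording, but that study is not at hand.
- *Leaving out the baseline score biases the result.* Randomisation protects the contrast. The loss is of precision and consistency.
- *The previous-4-weeks covariate is affected by treatment.* That would be possible only if it were recorded after randomisation. The timing is not stated, and Table 3 schedules the history questionnaire at baseline only, which favours a baseline reading without proving it.
- *The cost outcome rests on EQ-5D and cannot speak to affordability.* EQ-5D is mentioned as an additional source. The only costs compared are the separately collected direct costs, which do bear on affordability.
- *The absence of an incremental ratio or bootstrap interval is an error.* That is health-economic detail which a condensed article may leave to a fuller plan.

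**Conclusion.** The point holds as a correction to secondary analyses. The matching label and the confounding rationale are wrong for this design. The listed QoL model omits a baseline score that is already collected and conflicts with Table 5. EQ-5D has two unreconciled arm comparisons. The sentence on costs contradicts the article's own description of EQ-5D.

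The gain from including the baseline score is 9% to 49% of the variance against a model without covariates. It rests wholly on an assumed r of 0.3 to 0.7 and is smaller to the extent that the listed covariates already explain the 3-month score. The primary analysis and the non-inferiority decision are not touched.

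**What to change.** In Table 4:

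1. Analyse each 3-month QoL score by linear regression on treatment arm and the same score at baseline, with age, sex and socioeconomic status as prespecified prognostic covariates.
2. Delete the reference to matching and the confounding rationale, and put the text in the future tense.
3. Use the previous-4-weeks health-problems covariate only as measured at baseline. If it was not recorded then, drop it.
4. Make this model the single EQ-5D arm comparison, in place of the t-test on change, and align the wording of Tables 4 and 5.
5. Delete the sentence that economic costs can be calculated from EQ-5D. Take costs from the direct cost data and use EQ-5D only for the health effect.

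The cost is a change of wording and model specification. The QoL scores and direct cost data needed are already scheduled, so nothing new has to be collected.
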